##### US CF Registry Data

Within the period p, the index visit is defined as the first stable encounter visit at which an individual meets the eligibility criteria in the 2-year recruitment period. The follow-up visit is defined as the date of the stable encounter visit that is closest to 12 months after the index visit, but which falls within 9–15 months after the index visit. Individuals are included in the treatment group if they are recorded as being prescribed treatment at the index visit, as this is often assumed to be the treatment start date. Once an individual starts treatment, we assume they remain on treatment until the follow-up visit. Individuals are included in the control group if they are recorded as not being prescribed azithromycin at the index visit. Controls who are recorded as starting treatment at an encounter visit between the index visit and the follow-up visit are censored at the date of that encounter visit. For the US emulated trials, we also define the prior visit to be the most recent stable encounter visit prior to the index visit.

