Eligibility criteria	Include: French individuals diagnosed with CF (sweat chloride >60 mmol/L or a genotype known to cause the disease), aged 6–21 years, with the ability to perform pulmonary function tests with FEV_1_%>40 and the ability to swallow tablets.Individuals were excluded if they had the following: Allergy to macrolide antibiotics Long-term (>3 months) with macrolides during the 12-month period before study entry Liver disease with liver function tests >2 times the laboratory upper limit History of portal hypertension Kidney disease with serum creatinine >150 µmol/L and/or creatinine clearance <50 mL/min Use of any of the following in the 3 months before study entry: DNase, inhaled tobramycin, inhaled steroids	Individuals will be considered for inclusion if they have a clinically confirmed diagnosis of CF (ie, are present in the UK CF Registry) and have an observation date within the recruitment periods defined in section 4.3.1, aged between 6 and 21 years, and obtained FEV_1_%>40 on their pulmonary function test (taken on the day of the annual review). It is assumed that all individuals have the ability to swallow tablets.Exclusion criteria are as follows: Intolerance to macrolide antibiotics recorded at any time during study period. Prescription of chronic oral or prophylactic oral macrolides (including azithromycin) recorded at time 0. Acute liver failure with >3×the upper laboratory limit, INR>2, or not responsive to vitamin K at time 0 Recorded cirrhosis with portal hypertension at time 0. Serum creatinine levels >150 µmol/L at time 0. Prescription of DNase, inhaled tobramycin or inhaled corticosteroids recorded at time 0. No follow-up visit for time 1.	Individuals will be considered for inclusion if they have a clinically confirmed diagnosis of CF (ie, are present in the US CF Registry) and have an observation or encounter date within the time periods defined in section 4.3.1, aged between 6 and 21 years, and obtained FEV_1_%>40 on their pulmonary function test (taken on the day of the encounter visit). It is assumed that all individuals have the ability to swallow tablets.Exclusion criteria are as follows: As in the UK Emulated Trial As in the UK Emulated Trial Non--related liver disease recorded at time 0. Laboratory results from liver tests are not available in the US registry. Recorded cirrhosis at time 0. Portal hypertension is not available in the US registry. As in the UK Emulated Trial As in the UK Emulated Trial As in the UK Emulated Trial

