#### Main analysis

In the target trial, the authors investigated the change in FEV_1_% from baseline, with adjustment for baseline FEV_1_%. This is equivalent to a regression of the mean FEV_1_% at follow-up with adjustment for baseline FEV_1_%. We note that in the absence of imbalance between treatment groups in baseline FEV_1_%, the adjustment of baseline FEV_1_% is not required but may result in gains in efficiency. Both approaches result in estimates of the ATE as defined in equations(1)  (2).

In the emulated trials, we need to account for differences between treatment groups at baseline, including baseline FEV_1_%. We also require assumptions of positivity, no interference, consistency and conditional exchangeability (conditional on C). We use augmented inverse-probability-of-treatment weighting (AIPTW) to control for potential confounding by C. AIPTW involves defining models for the treatment and outcome. This approach was chosen as it is doubly robust, meaning that it gives consistent estimates of treatment effects if either the treatment model or outcome model is correctly specified.^27^ This represents an advantage compared with the alternative propensity score or outcome-regression based approaches which are singly robust.

The first step in implementing AIPTW is to estimate the propensity scores, that is, the probability of treatment conditional on baseline covariates:

(3)
PS=P(A=1|C)

Propensity scores will be estimated using logistic regression, including C as linear terms.

In the second step, we specify an outcome model conditional on treatment and covariates:

(4)
$$Y_{1}=\gamma_{0}+\gamma_{A}A+\gamma_{C}C+\varepsilon$$

The AIPTW estimator for

(5)
$$\hat{E}[Y_{1}(a)]=\frac{1}{n}\sum_{i=1}^{n}\left\{\frac{I(A_{i}=a)Y_{1i}}{\hat{P}(A_{i}=a|C_{i})}-\frac{I(A_{i}=a_{i})-\hat{P}(A_{i}=a|C_{i})}{\hat{P}(A_{i}=a|C_{i})}\hat{E}(Y_{1i}|A_{i}=a,C_{i})\right\}$$

where $\hat{P}(A_{i}=a_{i}|C_{i})$ can be obtained using predictions from the propensity score model. The estimator in equation 5 can be used to estimate $E\left[Y_{1}\left(0\right)\right]$ and $E[Y_{1}(1)],$ and the difference between these two expectations is an estimate of the average treatment effect in the population. Standard errors can be obtained based on the efficient influence function.^28^

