#### Allowing individuals to enter the emulated trials more than once

For the main analysis, individuals will be included in the emulated trial once. Individuals ‘enter’ the trial at time 0, which is defined as the earliest year within the recruitment period that they meet the inclusion and exclusion criteria. This approach restricts the analysis to using information from everyone at one time point only and may be inefficient. Alternatively, we can allow individuals to ‘enter’ the trial twice if they meet the inclusion and exclusion criteria in both years during the recruitment period. Standard errors will need to take into account that individuals are included multiple times.

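### US emulation: controls who start azithromycin are censored without any censoring adjustment, while treated patients are assumed never to stop, so the per-protocol estimand rests on two untested assumptions

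*Protocol article*

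**What the plan says.** The section US CF Registry Data defines the arms at the index visit: "Individuals are included in the treatment group if they are recorded as being prescribed treatment at the index visit". Controls are those recorded as not prescribed azithromycin at that visit. Later changes are handled differently by arm. For controls: "Controls who are recorded as starting treatment at an encounter visit between the index visit and the follow-up visit are censored". For treated patients: "Once an individual starts treatment, we assume they remain on treatment until the follow-up visit".

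Table 2 labels the emulated contrast per-protocol, against intention to treat in the target trial. The section Causal estimand of interest defines it as 12 months of azithromycin for everyone compared with none for anyone.

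The section Main analysis uses AIPTW "to control for potential confounding by C". Equation 3 is the probability of treatment given baseline C, equation 4 is an outcome model on treatment and C, and equation 5 combines the two. None has a term for remaining uncensored. The Data analysis section applies this plan to both registries.

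For lost outcomes, the Missing data section accepts complete cases if outcomes are missing at random given C, and otherwise says that multiple imputation may be considered. The Rationale section says that the article includes the statistical analysis plan.

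**The concern.** Censoring at a treatment change is a device for estimating a per-protocol effect. It works only if those who remain can stand in for those removed. The estimator adjusts for differences at time 0, but a control who starts azithromycin does so after time 0, possibly because of what has happened since. That information is not in C.

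If controls start because they have worsened, the removed controls are those with poorer 12-month FEV1%. The remaining controls then look too healthy. The double robustness claimed for AIPTW does not help: an outcome model on baseline C, fitted in uncensored controls, describes uncensored controls.

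In the treated arm, a patient whose prescription ends stays in the analysis as if treated for 12 months. If azithromycin works, this dilutes the effect. Both departures can pull the estimate down, and that estimate then goes into the three agreement criteria against the target trial.

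**Working it through.** **What the planned analysis needs**

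| Requirement of the estimand | What the plan does |
|---|---|
| Treated for 12 months | Assumed; no action on a recorded stop |
| Untreated for 12 months | Enforced by censoring controls who start |
| Censored controls represented by the rest | No censoring model; complete case if missing at random given baseline C |

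The plan therefore recovers its estimand under two conditions: (a) no treated patient stops, and (b) starting among controls is independent of the 12-month outcome given baseline C.

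**Inputs for size.** The article gives no start rates, stop rates or visit spacing, so all of these are assumptions:
- stable visits every 3 months;
- a 4% start probability per visit at average values;
- an 8% stop probability per visit, or none;
- baseline FEV1% with mean 80 and SD 18;
- an untreated 12-month change with mean -1.5 and SD 6;
- an effect proportional to time on treatment.

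The planned AIPTW was run on 1,000,000 simulated patients per scenario, with control starters dropped. The strength b is the rise in the log-odds of starting per 6 points lost since baseline. The standard error of each planned estimate is 0.03 to 0.07.

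| b | Controls censored | True effect 0, no stopping | True effect 3, no stopping | True effect 3, 22% stop |
|---|---|---|---|---|
| 0 | 11.6% | 0.01 | 3.01 | 2.66 |
| 0.3 | 12.6% | -0.12 | 2.88 | 2.54 |
| 0.6 | 14.8% | -0.26 | 2.74 | 2.42 |
| 1.0 | 19.1% | -0.49 | 2.51 | 2.24 |

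**Hand check at b = 0**
- Controls starting over three visits: 1 - 0.96³ = 11.5%.
- Treated stopping: 1 - 0.92³ = 22.1%.
- Mean share of the year on treatment with stopping: (1 + 0.92 + 0.846 + 0.779)/4 = 0.886, and 3 × 0.886 = 2.66, as simulated.
- Uncensored initiator contrast without stopping: controls spend (0 + 0.040 + 0.078 + 0.115)/4 = 0.058 of the year on treatment, and 3 - 3 × 0.058 = 2.82, as simulated.

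**Does weighting remove the shift?** A separate null simulation (400,000 patients, quarterly visits, 11–15% of controls censored) used log-odds of 0.05, 0.10 and 0.15 per point lost.

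| Log-odds per point | Complete case | Censoring weights | No censoring |
|---|---|---|---|
| 0.05 | -0.18 | -0.06 | -0.06 |
| 0.10 | -0.28 | 0.01 | 0.01 |
| 0.15 | -0.40 | 0.09 | 0.08 |

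The weighted results agree with the uncensored ones to within 0.01. Relative to no censoring, the complete-case shifts are -0.12, -0.29 and -0.48. The first two have the same strength as b = 0.3 and 0.6 above (0.05 × 6 and 0.10 × 6), where the shifts were -0.12 and -0.26.

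**Scale.** With an assumed SD of 10 and 500 versus 2000 patients, the emulation's standard error is 10 × √(1/500 + 1/2000) = 0.5. For the target trial (40 versus 42) the same SD gives 10 × √(1/40 + 1/42) = 2.2. A shift of 0.5 is then one emulation standard error, but moves the standardised difference between studies by only 0.5/√(0.5² + 2.2²) = 0.22, against the threshold of 1.96.

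**The case against.** Much of the case for the plan is fair. Continued treatment is an openly stated assumption. With that assumption and non-informative starting, the simulated plan returns the per-protocol value (3.01 for a true 3). C already holds FEV1%, its rate of decline, intravenous days and *P. aeruginosa*, so only dependence on change after baseline does harm. The Covariates section attributes prescribing to clinician and patient preference as well as clinical indication. The complete-case rule is conditional, with multiple imputation as a possible fallback. The Limitations section says that adherence data do not exist, and against the target trial's own uncertainty the shift is small.

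What this leaves standing: both conditions are strong and nothing in the plan tests them. A recorded prescription stop is a different datum from pill-taking, and the description of the US registry lists medication usage among the encounter data. The fallback does not name artificial censoring or post-baseline covariates. The significance criterion depends on the emulation's own standard error, where the shift is less negligible.

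Stronger readings that the documents do not support:

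- A reader might infer that "the index visit is defined as the first stable encounter visit at which an individual meets the eligibility criteria" turns most initiators into censored controls. The article gives no figure. With visits every 2 to 6 months and annual start probabilities of 5% to 30% (all assumed), censored controls are 46–83% of starters within 12 months of the index visit. Over the 24-month recruitment window they are 25–48%, because 41–49% start at or after follow-up and remain valid controls.
- A reader might call the first-visit rule an error that requires sequential trials from every visit. It is an efficiency choice. The plan acknowledges this and offers a sensitivity analysis in which individuals may enter "the trial twice if they meet the inclusion and exclusion criteria in both years during the recruitment period". No bias from the rule itself has been shown.
- A reader might want the uncensored initiation contrast as the main comparison because the target trial is intention to treat. Table 2 shows the difference openly. With about 95% adherence in the target trial, its two effects plausibly lie close together. The uncensored contrast gave 2.4 to 2.8 for a true 3.0, so making it the main comparison is a debatable trade-off.

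**Conclusion.** The concern holds in this form: the US per-protocol analysis handles treatment deviation in one arm only and has no adjustment for the censoring that it imposes. It estimates the stated estimand if no treated patient stops and starting among controls is independent of the outcome given baseline C. It would be too absolute to say that it can never be per-protocol.

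On the assumed rates, informative starting alone shifts the estimate by 0 to about -0.5 FEV1% points. With a true effect of 3.0, 22% stopping alone gives about 2.7, and stopping with strongly informative starting gives about 2.2. The downward direction assumes that worsening prompts starting, which is plausible but not documented. The actual size depends on registry data not shown. Severity: should-fix. Confidence: moderate.

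**What to change.** For the US per-protocol analysis:

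1. Define deviation symmetrically from recorded prescriptions: a start among controls and a recorded stop among treated patients. Censor both.
2. Fit the propensity model to everyone who enters at time 0. Model the probability of remaining uncensored at each encounter, by arm, with time-updated FEV1%, intravenous courses, *P. aeruginosa* and inhaled antibiotics. Multiply the treatment weights by the inverse of that probability, and use the censoring weights when fitting the outcome model too.
3. Use standard errors that account for the estimated censoring weights, and add those weights to the planned diagnostics.
4. Report the uncensored initiator versus non-initiator contrast as a sensitivity analysis alongside, since the target trial is intention to treat.
5. Tabulate by arm how many controls start and how many treated patients stop, so that readers can judge the size of the problem.

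The cost is additional modelling of data already held and somewhat wider intervals. The weights assume that the recorded variables capture the reasons for starting and stopping. Because the plan uses stable visits only, the intravenous treatment dates matter here.

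Two related passages need reconciling at the same time. The censoring list for time to intravenous antibiotics (Secondary outcomes) does not mention starting azithromycin. The Table 2 exclusion, "Prescription of chronic oral or prophylactic oral macrolides (including azithromycin) recorded at time 0", applied to the US by reference, conflicts if read literally with a treated group defined by prescription at the index visit, although the wash-out in Table 3 suggests that use before entry was meant.

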### Inclusion and exclusion criteria

Table 2 summarises the inclusion and exclusion criteria for the target and emulated trials. The data on liver function test results and serum creatinine levels (exclusion criteria 3 and 5) may have large amounts of missingness and therefore be unusable. An alternative is to use indicator variables for any recorded non-CF-related liver disease (for exclusion criteria 3) or chronic kidney disease (for exclusion criteria 5).

### Variables

#### Treatment strategies

The active and comparator treatment strategies used in the target trial are provided in table 2. We aim to match these strategies as closely as possible; however, the target trial specifies doses and frequency of treatment, and this information is not available in the UK or US CF registries.

For both the UK and US emulated trials, the active treatment is prescription of prophylactic oral or chronic oral azithromycin and the comparator is no prescription of prophylactic oral or chronic oral azithromycin.

#### Outcomes

Where possible, the emulated trials will replicate outcomes studied in the target trial; however, data are not available in the registries for all secondary outcomes. The primary outcome in the target trial, and both emulated trials, is absolute FEV_1_% at time 1. Secondary outcomes in the target trial include: number of pulmonary exacerbations, forced vital capacity (FVC), nutritional status with body mass index (BMI) z-score, the use of antibiotics, modifications of microbiological analysis of sputum or throat cultures and quality of life. Secondary outcomes in the emulated trials include:

Prescription of intravenous antibiotics at time 1 (as a proxy for pulmonary exacerbations).Percent predicted FVC at time 1.BMI z-score at time 1.

For the emulated trials, FEV_1_% will be calculated using the Global Lung Initiative (GLI) 2012 equations^25^ and BMI z-scores will be calculated using the WHO reference distribution.^26^

#### Covariates

In the target trial, individuals were randomly allocated to the treatment or placebo strategy. In the emulated trials, there is no randomisation. The data on treatment use within the UK and US CF Registries reflects treatment decisions made based on clinical indication and on clinician and patient preference. Being prescribed azithromycin is, therefore, assumed to be informed by a number of factors, many of which are also associated with the outcomes of interest. The association between prescription of azithromycin and FEV_1_% (and secondary outcomes) is, therefore, believed to be confounded by the following factors: age, number of days on intravenous antibiotics (intravenous days), non-intravenous hospital admissions, presence of *Pseudomonas aeruginosa*, *Staphylococcus aureus* or Nontuberculous Mycobacteria, pancreatic insufficiency, CF-related diabetes (CFRD), use of hypertonic saline or inhaled antibiotics and rate of decline in FEV_1_%, BMI z-score and FEV_1_%. These are depicted in a directed acyclic graph in figure 2.

**Figure 2 F2:**
[figure not shown]
Directed acyclic graph depicting assumed confounding relationships for the association between azithromycin at time 0 (azithromycin0) and FEV1% at time 1 (FEV1%1). U represents any unmeasured confounders. Subscripts denote time; 0* indicates prebaseline. BMI, body mass index; CFRD, cystic fibrosis-related diabetes; FEV_1_, forced expiratory volume in 1 s; NTM, nontuberculous mycobacteria; ppFEV_1_, per cent predicted FEV1.

Age, FEV_1_% and BMI z-score are continuous. Rate of decline in FEV_1_% is calculated as the difference between the absolute FEV_1_% measured at the index visit and the prior visit. Data on treatment prescription, the presence of infections, CFRD diagnosis, pancreatic insufficiency and non-intravenous hospital admissions will be binary indicators. Indicators for pancreatic insufficiency and non-intravenous hospital admissions are created using existing variables in the data. Registry data provide dates for treatment with intravenous antibiotics (at home or hospital). These data will be used to create a variable indicating the number of days on intravenous antibiotics since the last annual review (including treatment administered at home and hospital). Intravenous days will then be treated as a categorical variable with four categories: 0, 1–14, 15–28, 28+.

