## Data sources

### UK CF registry

The UK CF Registry was established in 1995 and is a national database sponsored and managed by the CF Trust, with UK National Health Service research ethics approval. It records longitudinal data on approximately 99% of people with CF in the UK.^17 18^

Data are collected on time-invariant variables, such as sex at birth, cystic fibrosis transmembrane conductance regulator (*CFTR*) genotype, date of birth, diagnosis data and longitudinal variables that change over time. Longitudinal data are collected at approximately annual review clinic visits on over 250 variables covering several domains. These include clinical measurements taken on the day, and other variables covering the previous 12 months period such as: hospital admissions, treatments prescribed, culture and microbiology, health complications, nutrition, physiotherapy, smoking and outcomes (death and transplants). In 2016, the UK CF Registry started collecting treatment prescription start and stop dates.

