### US CF registry

The US CF Registry began collecting data on people with CF in the USA in 1986 and is managed by the CF Foundation. It contains longitudinal information on approximately 80% of people with CF in the USA.^19^,^21^

Data are collected on demographic characteristics and on longitudinal variables that change over time. Data collection takes place at ‘encounter visits’ at CF care centres, with data also being abstracted annually. This study will use the encounter visit data which includes relevant information regarding hospitalisations, clinical measurements, medication usage, culture and microbiology, health complications. The encounter visits include routine clinical visits and visits in a hospital or the individual’s home. The non-routine hospital and home intravenous visits may be due to an individual experiencing worsening of their respiratory symptoms, and therefore, their lung function may be unstable at this time. These are referred to as ‘unstable’ visits, whereas routine clinical visits are referred to as ‘stable’ visits. The analyses in this study will use data from the stable visits only.

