### Setting

#### Time periods

The target trial was conducted from 2001 to 2003, with results published in 2006. Within the data collection period for the target trial, results from other azithromycin RCTs were published,^22^,^24^ after which there was uptake of this treatment in routine clinical practice. We plan to emulate the trial using data from three time periods of 3 years’ duration: 2003–2005, 2007–2009, 2016–2018. Period 1 is close to the timing of the target trial while allowing time for the treatment to have come into use. Periods 2 and 3 were chosen based on features of the data, and ending the time frame in 2018 means that we only use data from the time before CFTR modulators became widespread in clinical practice.

Table 3 provides further details and justification about the three time periods. For each 3-year time period, the first 2 years are used as the ‘recruitment period’, defined as the period during which individuals are considered for inclusion in the emulated trial. The target trial recruited participants over 2 years. Individuals are included in the emulated trial data if they meet the inclusion and exclusion criteria in at least one of their visits during the recruitment period.

**Table 3 T3:** Description of the time periods considered in the UK and US registry data

Time period	Justification for time period	UK data	US data
2003–2005	Closest time period to the target trial, allowing a couple of years for use of azithromycin to uptake in clinical practice.This will only be conducted using the UK data as the US registry did not collect data on azithromycin use during this time.	✓	×
2007–2009	The US registry started collecting data on azithromycin in 2006 and a 1-year wash-out period is required to select individuals who were not taking azithromycin prior to study entry. Therefore, this time period is as close to the time period used in the target trial as is possible for the US registry.	✓	✓
2016–2018	The UK registry started collecting data on treatment prescription dates in 2016. Therefore, this time period is a more recent period that predates widespread use of CFTR modulators but also allows use of treatment date data.	✓	✓

CFTRcystic fibrosis transmembrane conductance regulator

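### The US rate of FEV1% decline has no time in it and IV days have no fixed look-back, so two named confounders are not comparable between people

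*Protocol article*

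**What the plan says.** The Covariates section names both rate of decline in FEV1% and days on IV antibiotics as confounders of azithromycin prescription and outcome. It then fixes how each is derived.

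- **Rate of decline.** "Rate of decline in FEV_1_% is calculated as the difference between the absolute FEV_1_% measured at the index visit and the prior visit".
- **Prior visit.** This is defined once, under US CF Registry Data: "For the US emulated trials, we also define the prior visit to be the most recent stable encounter visit prior to the index visit". No minimum or maximum gap is given. The same section limits the follow-up visit to 9–15 months after the index visit. The UK section defines an index and a follow-up visit but no prior visit.
- **IV days.** The variable is the "number of days on intravenous antibiotics since the last annual review", grouped as 0, 1–14, 15–28 and 28+.
- **Visit spacing.** For the UK, "Longitudinal data are collected at approximately annual review clinic visits on over 250 variables covering several domains". For the US, "This study will use the encounter visit data which includes relevant information regarding hospitalisations, clinical measurements, medication usage, culture and microbiology, health complications", and the index visit is the first eligible stable encounter in the recruitment period.

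The Data analysis section applies one plan to both registries. Main analysis enters the confounders as linear terms in the propensity model (equation 3) and in the outcome model (equation 4). The Rationale and background section says that the article contains the statistical analysis plan, so these are stated derivation rules and not details left for later.

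**The concern.** A rate needs a time unit, and this one has none. In the UK the omission matters little if the prior visit is taken to be the previous annual review, because the gap is then about a year for everyone. In the US the gap is whatever separates two consecutive stable encounters, and elapsed time is not in the confounder list. The variable therefore mixes changes over different lengths of time under one coefficient, and does not measure the trajectory that the plan names as a confounder.

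The IV variable has a related fault. An annual review is a natural anchor when the index visit is itself an annual review. It is not one when the index visit is an encounter. The US section describes encounter visits and annual abstraction of data, but no annual review visit, so the anchor is at best variable and at worst undefined.

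The Covariates section says that prescribing reflects clinical indication, and Main analysis rests on exchangeability given the listed confounders. If recent decline and IV burden are measured differently from person to person, part of the confounding by indication stays in the estimate. Because this arises mainly in the US, it also adds an unplanned reason for the UK and US results to differ.

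**Working it through.** The plan gives no figure to reproduce. The check sets the definitions side by side and illustrates what they do. The gaps, FEV1% changes, SDs and IV rate below are assumptions, because the article gives no US visit spacing.

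**1. The undivided difference.** Let D = index FEV1% − prior FEV1%, and let m be the gap in months. The annualised change is D × 12/m. For D = −2 points:

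| Gap m (months) | Covariate as written | Annualised change (points/year) |
|---|---|---|
| 1 | −2 | −24 |
| 3 | −2 | −8 |
| 6 | −2 | −4 |
| 12 | −2 | −2 |

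Conversely, a true decline of 2 points/year gives an expected fall of 2 × m/12 = 0.17, 0.5, 1.0 and 2.0 points at 1, 3, 6 and 12 months.

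**2. What the linear models still control.** With index FEV1% (F0) and D = F0 − Fp both in the linear predictor, where Fp is prior FEV1%:

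b1·F0 + b2·(F0 − Fp) = (b1 + b2)·F0 − b2·Fp.

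This is adjustment for the index and prior readings, so level is controlled. If the confounder is the slope D/t, with t in years and coefficient b, the coefficient needed on D is b/t, which changes with the gap. A single b2 cannot be right for all gaps.

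**3. Why division alone is not enough.** The reliability of a two-reading difference as a measure of slope is

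(SDslope × t)² / [(SDslope × t)² + 2 × SDerr²].

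Take SDslope from 2 to 4 points/year and SDerr from 3 to 5 points.

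- At t = 0.25: from 0.25/(0.25 + 50) = 0.5% to 1/(1 + 18) = 5.3%.
- At t = 1: from 4/(4 + 50) = 7.4% to 16/(16 + 18) = 47.1%.

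Dividing by time corrects the scale, but short gaps remain mostly noise. A window on the prior visit is needed as well.

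**4. IV look-back.** Counted days = yearly rate × months/12. At a steady 28 days/year:

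| Look-back (months) | Days counted | Category |
|---|---|---|
| 1 | 2.3 | 1–14 |
| 3 | 7 | 1–14 |
| 6 | 14 | 1–14 |
| 12 | 28 | both 15–28 and 28+ |

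The same IV burden changes category with the timing of the index visit. The last row also shows the overlap at day 28, which affects both registries.

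**The case against.** The strongest reply is the identity in step 2. Both models already adjust for the last two FEV1% readings, whatever the variable is called, so this is not a confounder left uncontrolled. That stands. It limits the defect to a common coefficient across unequal gaps, but does not remove it.

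The UK defence also stands for the most part. UK visits are about annual, so both variables span roughly a year. The UK faults are the undefined prior visit and the overlapping category.

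A reader might infer more than the article supports:

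- **That US decline is mis-measured 12-fold, or that half of prior-year IV days are lost.** The first needs gaps of 1 to 12 months. The second needs index encounters spread evenly between annual reviews. The article gives neither.
- **That leaving out sex, genotype and calendar year is an error.** Sex and genotype are named as held only for the UK; the US text mentions demographic characteristics. Nothing shows that either affects both prescribing and outcome. For calendar year, the article says that uptake followed publication of other trials, but each period recruits over only two years and no link to outcome is shown. Figure 2, which also defines the confounder set, is not visible here.
- **That linear terms call for splines or arm-specific outcome models.** The article's statement on double robustness is correct, and nothing in it shows curvature. This is a modelling preference.

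**Conclusion.** The point holds as a fault in the derivation rules. In the US emulation, rate of decline is a raw difference over an uncontrolled gap, and IV days have a look-back that varies by person. The UK prior visit is undefined, and day 28 belongs to two categories in both registries. The consequence is residual confounding by indication of unknown size and direction, mainly in the US, and reduced comparability between the two emulations. The tables above show how the definitions behave under assumed gaps and rates; they do not estimate bias in the treatment effect. The conclusion assumes only that US encounter spacing varies between people, which is consistent with the article setting a window for the follow-up visit.

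**What to change.** Apply the same rules in both registries:

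1. **Rate of decline:** index-visit FEV1% minus the stable FEV1% nearest to 12 months earlier, within 9–15 months, divided by the years elapsed. This also supplies the missing UK definition, and mirrors the window already used for follow-up.
2. **IV days:** count over the 365 days before the index visit. Use the index visit as anchor in both arms, including the UK prescription-date analysis. There, time 0 for treated people falls after the index visit, so anchoring on time 0 would give the arms different reference dates.
3. **Categories:** 0, 1–14, 15–28, 29+.

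The Covariates section says that the registries provide dates of IV treatment, and the FEV1% rule needs only visit dates, so no new data are required. The cost is a change of derivation wording and code. The downside is that people with no FEV1% in the 9–15 month window go to the missing-data step. Their number is unknown and should be reported by treatment group.
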